### Design

The study is a superiority parallel-group, randomised controlled trial (RCT) of a 7-day residential, multidisciplinary intervention (MTD programme), and individualised physiotherapy outpatient care (IP programme) with 3-month follow-up. Measurements will be taken at baseline, post-treatment (7-day MDT; 6-weeks IP) and 12-weeks. We considered including a sham control treatment group but felt in a well-motivated young military cohort this could have a negative impact on recruitment. Trial participants, assessors and clinical/research staff will be un-blinded to treatment allocation. The protocol will conform to the CONSORT (Consolidation of Standards of Reporting Trials) guidelines for non-pharmacological interventions [25], and principles of the Declaration of Helsinki [26].

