### Outcome measures

Outcome measures with proven validity and reliability have been selected based on those recommended for clinical trials of intra-articular FAI [53], and current practice in UK military rehabilitation [54]. Standardised instruments recommended by OMERACT-OARSI guidelines [55] will also be included. These guidelines require measures of pain, physical function and a global assessment of health related quality of life. Participants will be assessed at baseline, on completion of treatment (1-week MDT group; 6-weeks IP group) and 12-weeks follow up (Fig. 1). The follow-up time-frames are the same for both groups (12-weeks), and all participants will be assessed at baseline and 12-weeks on the same clinical outcome measures. The inclusion of post-treatment measures may help reveal if any differences occur as a consequence of the different interventions (e.g., the immediate post-treatment scores by group). All outcome measures will be conducted, administered and overseen by the same supervising therapist on each occasion. Outcome measures used in the study are summarised in Table 4.

**Table 4 Tab4:** Summary of outcome measures

Primary outcome measure^a^	Data collection instrument
Function in daily living	Subscale of HAGOS
Physical function, activity level	Subscale of HAGOS
Hip symptoms, numeric pain rating	Subscale of HAGOS, subscale of NAHS, VAS
Secondary outcome measures^a^	
General health status	EuroQol -5D (EQ-5D-3 L)
Mood, anxiety, depression	HADS
Objective functional performance	6-minute walk test
Hip range of motion	Clinical methods and goniometry
Dynamic balance/postural control	Modified Star Excursion (Y-Balance) Test
Hip muscle strength	Hand held dynamometry
Treatment efficacy & self efficacy	SIRBS
Adherence to home-based exercise	Training Diary and 11-point rating scale
Patient demographics & past treatment	Questionnaire

^a^The primary end-point for data analysis is 3-months. All measures will be taken at baseline, post-treatment (1-week MDT group; 6-weeks IP group), 3-months with the exception of patient demographics which will only be assessed at baseline

*HAGOS* Copenhagen Hip and Groin Outcome Score, *NAHS* non-arthritic hip score, *VAS* visual analogue scale, *HADS* hospital anxiety and depression scale, *SIRBS* sports injury rehabilitation beliefs survey

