### Sample size

The primary endpoint will be change from baseline to 12-weeks in (a) the HAGOS ‘physical function in daily living’ subscale and (b) VAS numeric pain rating. Sample size calculation is based on clinically relevant changes over the study period (e.g., score changes between baseline and follow-up should be, on average, subjectively perceptible by the participant). The minimum clinically important difference (MCID) in the HAGOS subscale has been suggested to be 4.8–5.2 points [53]. Between participant standard deviations have not been widely reported for the VAS using intra-articular hip pain patients [1, 10]. Therefore, the required sample using a MCID of 5.2 between groups on the HAGOS subscale and a standard deviation of 11 points, with a significance level of 0.05 (2 tailed) and a power of 80 %, is 43 per group. Allowing for an estimated drop out rate of approximately 15 % at the 12-week follow-up, a total of 100 participants will be recruited into the study. Based on current referral rates it is anticipated this sample target will be met from routine referrals to DMRC Headley Court and no additional strategies to promote enrolment are required. The sample size was calculated using G*Power software Version 3.0.10 (Franz Faul, Universitaet Kiel, Germany). There is currently no RCT reporting the effects of a residential MDT intervention versus outpatient individualised treatment approaching this sample size in the available literature.

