### Statistical analysis

The statistical analysis will be undertaken in accordance with the intention-to-treat (ITT) principle. The ITT analysis will include all participants, including those who do not fully adhere to the protocol and those with missing outcome data. A per-protocol analysis will also be performed where appropriate. Demographic and clinical characteristics as well as baseline data will be presented to assess the baseline comparability of the two groups. Differences from baseline to each time point will be calculated for all primary and secondary outcomes. Descriptive statistics will be presented for each group as mean change, standard deviations and confidence intervals (CI) for continuous variables, and frequencies and percentages for categorical variables. A longitudinal repeated measures design will be used to assess changes from baseline, and to make between group comparisons for the continuous outcome measures. Between group comparisons will be made immediately post treatment (1 week residential group; 6 weeks outpatient group) and at 12 weeks.

The effect of the interventions over time will be compared using linear and mixed models. These models are chosen as they appropriately adjust for correlation that occurs from collecting multiple observations per participant [37]. At the 1,6 and 12 week time points, continuous variables will be analysed using a mixed model repeated-measure analysis of variance (ANOVA) model (with treatment as the between group factor and time as the repeated factor). The non-parametric equivalent or data transformation will be used if non-normal distributions apply. Where significant differences occur, post-hoc comparisons will be conducted using Tukey’s multiple comparison procedure. Differences in nominal/ordinal data will be analysed using the *χ*

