^2^ test. A significance level of 0.05 will be set for any inferential statistics conducted. The inclusion of the post treatment (T2) measure may help reveal if any differences occur as a consequence of the different interventions (as T2 reflects the immediate post-treatment scores for each group). However, this is based on the assumption that any changes in outcome from T1 and T2 (over 1 and 6-weeks) are linear, and also between T2 and T3. We recognise if the trend is non-linear then we will have insufficient data points to model the outcome over time in a way that will enable us to compare the trajectory of patient outcomes using the 3 time points. If interim analysis reveals this to be the case, we will remove T2 measures from the final analysis.

Secondary analysis will be undertaken to assess the predictors of outcome at the primary endpoint (12 weeks post treatment commencement) in both groups, using multiple regression analysis. Predictor variables including age, gender, baseline pain, physical function, duration of symptoms, mood/anxiety, self-efficacy, co-morbidities and exercise adherence will be measured. Analyses will be performed separately for MDT and IP group treatments. Response variables will be change in HAGOS function in daily living score pre and post intervention (MCID > 5.2 points) and numeric pain rating on the VAS. All predictors will be checked for collinearity. Univariate logistic regression will be performed on all potential predictors and those associated with the outcomes will be entered into the multivariate logistic regression model. Variables with the lowest predictive value will be removed from the model if *p* > 0.05. Odds ratios and 95 % CI’s will be calculated for all final predictors.

No statistical adjustment will be made for multiple testing. All tests will be two-sided and carried out at the 5 % level of significance. Changes to the study design or analysis plan will be documented with full justification. A statistician will oversee the blinded analyses of the data. The statistical analysis procedure will be discussed, reviewed and co-worked with statisticians at the Department for Health University of Bath, and School of Clinical Sciences at Bristol University.

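### If triggered, the rule to drop T2 discards the only post-baseline score of men who miss week 12 after completing T2, which undercuts the intention-to-treat statement

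*Protocol article*

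**What the plan says.** All statements are in the Protocol article.

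- Design sets three assessments: "Measurements will be taken at baseline, post-treatment (7-day MDT; 6-weeks IP) and 12-weeks". T2 is therefore at week 1 in the residential arm and week 6 in the outpatient arm.
- Sample size: "The primary endpoint will be change from baseline to 12-weeks in (a) the HAGOS" daily-living subscale, with VAS pain as its partner. The same section has "Allowing for an estimated drop out rate of approximately" 15% at week 12, and recruits 100.
- Statistical analysis, on the analysis set: "The ITT analysis will include all participants, including those who do not fully adhere to the protocol and those with missing outcome data".
- Statistical analysis, on the model: "continuous variables will be analysed using a mixed model repeated-measure analysis of variance (ANOVA) model (with treatment as the between group factor". The within-participant factor is time. The sentence opens "At the 1,6 and 12 week time points, continuous variables will be analysed", so baseline is not named as a response, although change from baseline is the endpoint.
- Statistical analysis, on T2: the section accepts that three points cannot describe a non-linear course, and continues "If interim analysis reveals this to be the case, we will remove T2 measures from the final analysis".

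**The concern.** A repeated-measures mixed model is a reasonable way to honour an intention-to-treat promise when some week-12 scores are missing. It uses each man's earlier scores and is valid if dropout depends only on what was observed. For a man lost between T2 and week 12, the informative earlier score is T2, because it already reflects his response to treatment. The removal rule takes that score out of the final analysis for a reason unrelated to missing data, namely that the trajectory may not be linear.

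The trigger is not remote, since the section itself allows for a non-linear course. If it fires and dropout is related to early response differently in the two arms, the week-12 contrast can shift. The arms differ in ways that make this possible: one finishes treatment in 7 days, the other attends 8 sessions over 6 weeks.

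**Working it through.** **1. How many men are affected.** On the plan's own figures, 100 × 0.15 = 15 men lack a week-12 score, leaving 85, or 42.5 per arm. The recruitment step is consistent with that rate: 86 / 0.85 = 102 and 86 × 1.15 = 99, against 100 stated. Only those of the 15 who reached T2 are touched by the removal rule. The article does not say how many that is.

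**2. What is left once T2 is removed.**

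| Form of week-12 analysis | Man with baseline and T2 but no week 12 |
|---|---|
| Change score, baseline to week 12 | No value; excluded |
| Week 12 with baseline as covariate | No response; excluded |
| Mixed model, baseline and week 12 both responses | Retained through baseline only; T2 information lost |

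The third row is not the same as completers only. In one simulated data set, the group-by-time estimate was 7.19 (SE 2.12) with all 100 men and 7.74 (SE 2.15) with the 89 completers.

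**3. Does keeping baseline as a response solve it?** Simulation assumptions: true effect 5.2, SD 11, 50 per arm, correlations 0.6 (baseline/T2), 0.6 (baseline/week 12) and 0.8 (T2/week 12), about 16% dropout acting in opposite directions in the two arms, 4,000 trials.

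| Dropout depends on | Completers' change | Baseline + week 12 model | All three waves |
|---|---|---|---|
| T2 | 4.5 | 3.6 | 5.2 |
| Baseline | 6.6 | 5.2 | 5.2 |

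When dropout depends on baseline, the model without T2 is unbiased. When it depends on T2, that model is off by 5.2 − 3.6 = 1.6 points, and the three-wave model is not.

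**4. Illustrative size with no true difference.** Assumptions: SD 11, 50 per arm, 15% lost per arm, residential loss random, outpatient loss logistic in the standardised T2 response with slopes 0.5 to 2.5, 4,000 trials per setting. The completers' bias is approximately

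bias ≈ ρ × SD × (shift in mean T2 among outpatient completers, in SD units).

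| T2/week-12 correlation ρ | Bias in completers (points, absolute) | Rejection at nominal 5% |
|---|---|---|
| 0.5 | 0.45 to 1.22 | 5.0% to 7.7% |
| 0.7 | 0.52 to 1.69 | 5.9% to 11.2% |

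Repeat runs of the same set-up widen this to about 0.3 to 1.7 points and 5% to 12%. As a share of the target, 0.3 / 5.2 = 6% and 1.7 / 5.2 = 33%. By the formula, these ends correspond to shifts of 0.3 / (0.5 × 11) = 0.05 SD and 1.7 / (0.7 × 11) = 0.22 SD.

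**5. How much T2 recovers.** Same set-up, predicting week 12 from T2 within each arm:

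| Outpatient dropouts who leave before week 6 | Remaining bias (points) |
|---|---|
| None | at most about 0.1 |
| Half | about 0.15 to 0.8 |
| All | 0.44 to 1.70, the same as completers |

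**The case against.** The strongest objection is that outpatient men who stop during their course of visits leave before week 6 and have no T2. Retaining T2 cannot help them and deleting it costs them nothing. This stands, and it is why step 5 gives a range: near-zero remaining bias needs every dropout to have reached T2.

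A second objection is that the handling of missing data is normally left to a statistical analysis plan, which is not shown and may specify imputation. That also stands, so the absence of an imputation method is not criticised here. The removal rule, however, is written in the article, and it works against the intention-to-treat statement in the same section. One could read it as barring T2 only as a modelled outcome and leaving it available for imputation. The sentence does not make that distinction.

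Third, differential, response-driven dropout is assumed, not documented. At the mild end of the simulation the false-positive rate stays at about 5%.

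A reader might infer three stronger things that the documents do not support:

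- That the primary result will become a complete-case analysis. Removal is conditional on the interim check, and baseline-only men still contribute if baseline is a modelled response.
- That bias could never be examined afterwards. T2 leaves the final analysis, not the database, and changes to each time point are to be calculated, so dropouts' T2 scores can still be compared with completers'.
- That men who cannot attend lose their questionnaires because "All outcome measures will be conducted, administered and overseen by the same supervising therapist on each occasion". That sentence describes who administers the measures. It does not say what happens to non-attenders.

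**Conclusion.** The point holds in a conditional form. If the interim check leads to removal, men who have T2 but miss week 12 lose their only post-baseline score, and the statement that participants with missing outcomes are included is weakened for the primary endpoint. It fails outright under a change-score or baseline-as-covariate analysis. It survives in part if baseline is a response, but the estimate can still be biased when dropout depends on T2.

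The size, about 0.3 to 1.7 points on a 5.2-point target, is illustrative. It rests on 15% loss, SD 11, T2-dependent loss in one arm only, and a T2/week-12 correlation of 0.5 to 0.7. Of these, only the 15% and the SD come from the article. The direction in a real trial cannot be predicted. The point is worth correcting because removal is unnecessary: a week-12 contrast that uses T2 does not require a linear course.

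**What to change.** Replace the removal sentence in Statistical analysis. State that, even if trajectories are not compared, T2 stays in the week-12 analysis in one of two ways:

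- as a repeated-measures response with time as a categorical factor by arm and week 12 as the primary contrast. The covariance should be allowed to differ by arm, because T2 is 12 − 1 = 11 weeks before the endpoint in one arm and 12 − 6 = 6 weeks in the other; or
- as an auxiliary variable in multiple imputation of week-12 scores, done separately within each arm.

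Neither route needs linearity, and for the week-12 result neither compares week 1 with week 6. Report the completers analysis as a sensitivity analysis. Say whether baseline is a response or a covariate, since step 2 shows that this decides who is retained. The cost is a little extra programming, with no new data collection. The limit is that men who leave before T2 are not helped, so report their number by arm.

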A definition of rehabilitation based on the concepts of structure and process is frequently used when assessing the content of health care interventions [32]. In our study the therapeutic content (e.g., exercise, manual therapy, education, home-based programme) is the same for both study groups. However, the structure and process will differ significantly. The residential arm is group treatment delivered by a MDT in a residential setting over 7-days. The outpatient arm is physiotherapist led individual treatment delivered during a series of weekly appointments over 6-weeks. Therefore, the amount of direct therapist contact, hands-on physical therapy and instructions surrounding exercise adjustment and education will differ. A detailed description of the treatment methods is contained in Table 3 and Additional file 1.

Eligible patients will be invited to participate in the study and complete an informed consent form. Patients agreeing to participate will be informed of treatment group assignment and referral arrangements by a civilian member of the clinical team, and all necessary study documents will also be provided. Ineligible patients will receive an ongoing referral in accordance with the existing UK military best practice care pathway. Following consent, participants will be consecutively randomised into either the residential or outpatient group by an independent administrator not involved in recruitment, assessment or treatment of participants. Baseline testing will be conducted immediately prior to commencement of treatment. Participants will be reassessed on completion of treatment (1-week (MDT); 6-weeks (IP)), and again at 12-weeks (week 12). During the 12-week follow up period, all participants will be advised to continue with an unsupervised home exercise programme. A log book record of exercise participation will be maintained during this period, and participants will be asked to refrain from seeking other treatments during the study.

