Group exercise	Strengthening exercises, active range of motion exercises, functional balance drills, gait drills, progressive co-ordination drills, non-weight-bearing aerobic/endurance exercise, minor team games.	Restore strength of deep hip stabilisers, improve core strength, increase joint range of motion, improve balance and neuromotor control, improve muscle endurance, promote group cohesion and social support.	12 (30–45 min)
Individual physiotherapy^a^	Manual therapy techniques, muscle activation and timing patterns, active and passive range of motion exercises, advice on home-exercise, gait re-education training.	Improve quality and timing of movement, improve muscle strength, reduce pain, increase joint range of motion, induce relaxation, promote normal walking gait.	5 (30 min)
Hydrotherapy/swimming	Non weight-bearing aerobic exercise, strengthening exercises, active range of motion exercises, self-paced recreational swimming, progressive/assisted weight-bearing exercise and activity.	Improve muscle strength, improve aerobic capacity, increase joint range of motion, improve confidence in weight-bearing, induce relaxation, promote enjoyment and variety of treatment.	3 (60 min)
Individual occupational therapy^b^	Relaxation techniques, postural re-education, cognitive behavioural therapy (CBT) techniques, self-help coping strategies, pain management.	Induce relaxation, promote behavioural change, control pain, correct/improve poor posture.	3 (60 min)
Patient education	Coping with pain, benefits of exercise, joint protection, anatomy and pathology of hip pain, nutrition.	Activity modification, reduction of pain, promotes behavioural change, weight management, improve knowledge of treatment options, improve ability to relax, improve knowledge of self-help techniques.	2 (60 min)

^a^Exercise dosage, progression and intensity will be governed by the physiotherapist and tailored to the needs of each individual patient; ^b^Occupational therapy referrals will be individually prescribed to selected patients

**Table 3 Tab3:** Overview of Outpatient Individual Programme (IP Group) and Residential (MDT Group) Study Treatment Schedule

Outpatient (IP) Protocol	Residential (MDT) Programme
Session 1 (45–60 mins)^a^	Day 1
• Subjective and objective assessment (20–25 mins)	• Admission MDT clinic and baseline measures
• Patient education (5-mins)	Day 2
• 1–2 manual therapy techniques (5–10 mins)	• Group-based introduction to treatment goal 1

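### A randomised participant who never starts treatment has no scheduled baseline and no defined week-12 date, although the ITT analysis is said to include everyone

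*Protocol article*

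**What the plan says.** All statements are in the protocol article.

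- **Allocation (Procedure).** "Following consent, participants will be consecutively randomised into either the residential or outpatient group by an independent administrator". The section on randomisation and concealment adds that the envelope is opened once eligibility and consent are complete. Participants are then told their arm.
- **Baseline (Procedure; Table 3).** "Baseline testing will be conducted immediately prior to commencement of treatment". For the residential arm, Table 3 lists "Admission MDT clinic and baseline measures" on Day 1 of the stay. A footnote to outpatient Session 1 says that its timing leaves out the baseline outcome measures. The assessment clinic is described only as establishing eligibility, and no outcome measurement is described there.
- **Endpoint (Sample size).** "The primary endpoint will be change from baseline to 12-weeks", for the HAGOS daily-living subscale and VAS pain.
- **Clock (Statistical analysis).** The secondary analysis concerns "predictors of outcome at the primary endpoint (12 weeks post treatment commencement) in both groups".
- **Derived outcome (Statistical analysis).** "Differences from baseline to each time point will be calculated for all primary and secondary outcomes".
- **Analysis set (Statistical analysis).** "The ITT analysis will include all participants, including those who do not fully adhere to the protocol and those with missing outcome data".

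**The concern.** Both ends of the primary measurement, the baseline and the week-12 visit, hang on an event that comes after randomisation and that some randomised participants may never reach. The schedule gives such a participant nothing to measure change from and no date on which to be measured. The promise to analyse everyone then has no data to work on for him, unless someone improvises.

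This matters because any loss between allocation and start happens when the arm is known. The arms ask for different things: a week in residence, or 8 sessions over 6 weeks. Failure to start could therefore differ by arm and be related to prognosis. If so, a comparison that in practice rests on those who started is no longer fully protected by randomisation. The Discussion names randomisation and intention-to-treat among the features that limit bias, so the point touches a stated strength of the design.

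**Working it through.** **Step 1: follow a non-starter through the schedule.**

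| Element | What the article ties it to | Value for a non-starter |
|---|---|---|
| Allocation | consent, then envelope | known |
| Baseline score | just before treatment; residential Day 1 | none scheduled |
| Change score | week-12 score minus baseline | cannot be formed |
| Week-12 date | treatment commencement | undefined |
| Place in the ITT set | all participants | promised |

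The parenthesis that fixes the clock sits in the paragraph on predictors, but it describes the primary endpoint and agrees with a baseline taken at treatment start. The Procedure and Home-based programme sections also speak of a 12-week follow-up period for home exercise prescribed at the last treatment session. That reading is tied to treatment as well, so it gives a non-starter no date either.

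**Step 2: the plan's own figures.** The article gives no rate of non-starting. The nearest figure is the allowance of about 15% dropout by week 12. Applied to the stated 43 per group, 43 / (1 − 0.15) = 50.6, so 51 per group or 102 in all, close to the stated 100. That allowance covers dropout at follow-up, not failure to start, so it serves only as an outer limit for the non-start share. The 43 itself does not follow from "a MCID of 5.2 between groups on the HAGOS subscale and a standard deviation of 11 points": a two-sided two-sample t-test at 5% and 80% power needs 72 per group. That is a separate matter and does not bear on this point. Here 5.2 and 11 are used only as yardsticks.

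**Step 3: size of the possible shift.** Let s be the non-start share in an arm, and g the difference in mean outcome between non-starters and starters.

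- Mean of all randomised in the arm = (1 − s) × starters' mean + s × non-starters' mean.
- So mean of all − mean of starters = s × g.
- With the same g in both arms, the between-group difference moves by (s₁ − s₂) × g, the excess share times the gap.

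Both inputs are assumptions. The excess runs from 0 to 15%. The gap runs from 5.2 points (one MCID) to 11 points (one SD).

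| Excess in one arm | Participants of 50 | Shift, g = 5.2 | Shift, g = 11 | Share of 5.2 |
|---|---|---|---|---|
| 0% | 0 | 0 | 0 | 0% |
| 5% | 2.5 | 0.26 | 0.55 | 5–11% |
| 10% | 5 | 0.52 | 1.10 | 10–21% |
| 15% | 7.5 | 0.78 | 1.65 | 15–32% |

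The last row puts the whole dropout allowance into non-starting as an excess in one arm. Its upper end also needs a gap of a full SD.

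**The case against.** The strongest reply is that the intention is stated correctly and only its operation is missing. The article includes non-adherers and those with missing outcomes, and says that all participants are assessed at baseline and 12 weeks. Missing-data handling commonly sits in a full protocol or analysis plan, and neither is shown. This stands in part: an imputation rule is not owed here. But the article itself fixes when data are collected, and no analysis plan can recover a baseline that was never taken. Table 4 says that demographics, too, are collected only at baseline, so even the covariates for imputation may be absent.

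A reader might infer that the plan excludes non-starters, or that its ITT analysis is by construction one of starters only. The documents do not support that. No passage excludes them. If the mixed model takes the score at each visit as its response, a week-12 value can enter without a baseline. What is missing then is a date and an arrangement for collecting that value.

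The number affected may also be small. The article gives neither the place of randomisation nor the interval before treatment, and the flow diagram is not available. Eligibility requires enough time to attend for therapy, and patients are told of both arms before they come to the clinic. These safeguards make non-starting less likely. They do not say what happens when it occurs.

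**Conclusion.** The point holds as a conflict between the measurement schedule and the promised analysis set. Under the schedule as written, a non-starter has no scheduled baseline, no change score and no defined week-12 date.

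The size is unknown and may be nil. An assumed 5% excess in one arm with a gap of 5.2 to 11 points gives about 0.3 to 0.6 points. The 1.65 points at 15%, about a third of the target difference, should not be read as an expected bias: it joins the largest assumed excess to the largest assumed gap, and neither figure is in the article.

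The change is worth making before recruitment because it is cheap and a missed baseline cannot be restored later.

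**What to change.** 1. Have every participant complete the self-report primary questionnaires (HAGOS, NAHS and the VAS on paper) at the clinic, after consent and before the allocation envelope is opened. Use that one value as baseline for both arms in the ITT analysis, so that starters and non-starters are measured from the same point. Keep the treatment-start session for the physical tests.
2. Give every randomised participant a week-12 date that does not depend on starting: 12 weeks from the scheduled start date, or from randomisation if none was booked. Post the paper questionnaires to non-starters. Paper matters because the VAS is a 100 mm line.
3. Define the ITT set as all randomised participants by allocated arm, and report the number of non-starters by arm.

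The cost is one short extra questionnaire set at a visit that already takes place, a self-report baseline somewhat earlier than treatment start, and postal follow-up of probably a few people. Postal collection departs from the rule in Outcome measures that one supervising therapist oversees every assessment, so the protocol should state the exception.
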